### Primary outcome measure

2.5.

The primary outcome is the incremental cost-utility ratio estimated at 24 months between two treatments strategies for chronic long bone osteomyelitis.

### Secondary outcome measure

2.6.

Secondary outcomes are classified as efficacy secondary outcome measures or economic secondary outcome measures.

#### Efficacy secondary outcome

2.6.1.

- Proportion of patients with at least one recurrence of infection on the studied bone at 24 months (confirmed by the event validation committee) and time to recurrence;- Number and types of intraoperative and postoperative complications up to 24 months (including fracture) according to CTCAE and Clavien-Dindo classifications; and proportion of patients with at least one complication during follow-up;- Number of repeat surgeries for complication up to 24 months; and proportion of patients who had at least one repeat surgery for complication during follow-up;- Proportion of patients with amputation of the area containing the bone studied at 24 months;- Proportion of patients with bone healing and proportion of patients with bone remodeling/consolidation at 12 months, assessed from a standard radiograph (confirmed by the Clinical Event Validation Committee);- Number and types of serious adverse events (SAEs) attributable to systemic antibiotic therapy following the first intervention; and proportion of patients with at least one SAE attributable to this systemic antibiotic therapy; within 3 months of the first intervention;- Proportion of patients with acute renal failure within 3 months of the first procedure;- Number and types of adverse events related to the use of Cerament-G (e.g., hypercalcemia, serous discharge prolonged by scarring, heterotopic ossification, allergies) occurring within 3 months after the first procedure.

#### Economic secondary outcome measures

2.6.2.

- Cost of both strategies estimated at 24 months;- Cost of a corticotomy procedure using Cerament-G;- Estimated utility based on the Euroqol EQ-5D questionnaire and on utility scores validated on the French population at inclusion, at S + 4/S + 6, M3, M6, M12, M18 and M24 (usual follow-up visits) as well as after each repeat surgery according to the same schedule;- Incremental cost-effectiveness ratio estimated at 24 months with no recurrence of infection as efficacy outcome measure;- Budget impact analysis carried out from the perspective of the French Health Insurance.

### Health economic evaluation

2.7.

#### Main characteristics of the evaluation

2.7.1.

Given the working hypotheses, and in accordance with the recommendations of the French National Health Authority (14), the cost-utility study will be conducted from the collective perspective.

A time horizon of 24 months after the initial surgery will be used, which allows to take into account most important costs associated with the surgery and its consequences. Costs and results will be discounted using a 2.5% rate.

#### Cost evaluation

2.7.2.

The cost assessment will take into account hospitalizations (complete or day) in medicine, surgery, obstetrics, follow-up and rehabilitation care and at home, biological and radiological examinations, consultations of a general practitioner or a specialist (infectious disease specialist, orthopedic surgeon, etc.), nursing and physiotherapy care, consumption of drugs (analgesics and antibiotics), transport of patients, professional home help and informal care.

These costs will be valued using production cost or, if not possible, according to the corresponding tariff. The replacement cost approach, also known as “proxy good method,” will be used to value informal caregiver time. This approach assumes that any informal helping activity can be done by a worker in the market. According to this principle, each activity is valued according to what it costs in the labor market. One hour of help will therefore be valued at the average hourly wage of a professional help (15, 16).

For patients’ hospital stays, data will be collected from medical information departments of each participating center.

The number of subjects included in the study is relatively small and these patients are provided with follow-up regularly in hospital. In addition, the patient will need to enlist the cooperation of his/her caregiver to complete the data on informal care, based on an adaptation of existing questionnaires (17, 18). For these reasons, a booklet will be given to the patient on discharge from hospital to collect the consumption of outpatient resources as well as the data necessary for the evaluation of professional and informal help.

Corticotomy surgery incorporating the use of Cerament-G is an innovative procedure whose production cost has never been evaluated and for which no tariff is available since it is not currently reimbursed by the French Health Insurance: a micro-costing analysis will therefore be performed. Since the cost of corticotomy surgery without the use of Cerament-G is known, we will focus on the additional resources consumed when using Cerament-G, i.e., the medical device, the additional duration of use of the operating room, the staff time required for the preparation and injection of Cerament-G. The data needed to estimate these costs will be collected in the study’s case report form. Block occupancy and staff time will be valued from cost accounting, and the medical device from its non-negotiated acquisition price.

#### Measurement of the result in the medico-economic evaluation (primary outcome measure)

2.7.3.

The outcome criterion for the main medico-economic evaluation will be the number of Quality Adjusted Life Years (QALY).

In accordance with the recommendations (14), QALYs will be estimated from the responses to the Euroqol EQ-5D questionnaire. We will use the 5-Level version with the preference scores validated on the French population (19).

We hypothesize that the EQ-5D questionnaire will be sufficiently sensitive to variations in quality of life. However, as a precaution a secondary cost-effectiveness study will be conducted, with freedom from recurrence of infection at 24 months as the clinical outcome.

#### Presentation and interpretation of results

2.7.4.

Once the cost and the number of average QALYs per patient have been calculated for each of the two strategies studied, the results will be represented in a cost-utility plan. This graph, which represents the cost differential on the x-axis and the utility differential on the y-axis, shows whether one of the two strategies is dominated. If the innovative strategy is less costly and more effective than the standard of care, it will be efficient. Conversely, if it is more costly and less effective, we can conclude that it is not efficient. In all other cases, we will have to relate the two dimensions of cost and utility by estimating the incremental cost-utility ratio.

If the innovative strategy is less costly and less efficient, the ratio will provide information on the reduction in efficiency that must be made in order to reduce costs. If the innovative strategy is more costly and more efficient, the ratio will provide with information on the additional cost generated by the innovative strategy compared to the standard of care per QALY gained. In the latter case, an acceptability curve will be constructed, representing the probability that the innovative strategy is cost-effective compared to the standard of care, as a function of the collectivity’s willingness to pay (in other words of the value assigned by the collectivity to a QALY). It will make it possible to visualize the intervention that maximizes the net benefit according to the accepted thresholds of acceptability.

#### Budget impact analysis

2.7.5.

If the innovative strategy proves to be efficient, a budget impact analysis (BIA) is planned. In France, when a medical device enters into common law, the results of the BIA, like those of the medico-economic evaluation, can be used by the Economic Committee for Health Products when negotiating the price with the manufacturer.

The objective of the BIA in the CONVICTION study will be to estimate the impact of the introduction and dissemination in the French health system of the innovative strategy in the treatment of chronic osteomyelitis of long bone. The BIA will therefore provide information to decision-makers on the financial sustainability of this innovation, which will complement the information on efficiency provided by the medico-economic evaluation.

In accordance with the recommendations of the French National Authority for Health (20), the BIA will be carried out from the perspective of French Health Insurance. A 5-year time horizon will make it possible to take into account the gradual substitution of the standard of care by the innovative strategy using Cerament-G.

### Data collection

2.8.

The study data will be collected in an electronic case report form (eCRF). This eCRF, specific to the study, will be developed by a data manager from the Hospices Civils de Lyon using Ennov Clinical® 7.5.720 software. This software complies with the recommendations of the FDA on computerized systems for the management of clinical trials (Guidance for Computerized Systems Used in Clinical Trials) as well as the recommendations of the FDA on the electronic signature (21CFR part 11).

The CRF will only include the data necessary for carrying out the protocol and for scientific publication. The other patient data necessary for their follow-up outside of this study will be collected in the patient’s medical file.

### Safety and adverse events monitoring

2.9.

All adverse events occurring within the study, from inclusion, will be recorded in the eCRF and will be graded according to the Clavien-Dindo scale and/or the Common Terminology Criteria for Adverse Events (CTCAE). The investigator will determine causality in relation to the study, the procedure and/or the use of the device. All adverse events with great intensity, life threatening and death (i.e., ≥3 on the CTCAE and ≥ 3a on the Clavien-Dindo scale) will be considered serious and notified to the sponsor.

As Cerament-G is CE-marked and used in accordance with the manufacturer’s Instruction For Use, all incidents and risk of incidents will be notified to the sponsor and to the French Agency for the Safety of Health Products *via* the local material surveillance correspondent of the participating center.

### Statistical considerations

2.10.

#### Sample size calculation

2.10.1.

The sample size calculation has been based on the most relevant clinical efficacy outcome measure, which is the proportion of patients with at least one recurrence of infection at 24 months.

Available data show rates of 4 to 5% when using Cerament-G, for durations between 5 and 21 months (10, 11); as the follow-up is longer in the CONVICTION study (24 months), the hypothesis chosen was a rate of 6%. On the other hand, the proportion of recurrence of infection in the standard of care is estimated at 20% (21). The total number of patients to be randomized in the study will be 200 (100 per group; considering alpha-risk at 0.05, power of 80% in a bilateral situation and approximately 10% of early withdrawal).

The estimate of the number of subjects needed according to medico-economic hypothesis would require numerous hypothesis, leading to uncertainty. Only the cost of Cerament-G and hospitalizations for recurrence of infection, and the impact on the short-term utility of the surgery for recurrence of infection (6% in the innovative strategy vs. 20% in the standard of care), fractures and amputations (5% in both groups) have been taken into account. We hypothesize that the utility is decreased 6 months before revision surgery, 3 months after revision surgery, 9 months after amputation and 3 months after fracture. As no utility data are available in the literature for “before surgery” and “after surgery” conditions, they have been estimated according to expert opinion. As little data is available in the literature for health states comparable to the health states “after fracture” and “after amputation” and for the sake of homogeneity of the measurement, the utility concerning these states has also been estimated by expert opinion. However, these data seem consistent with the closest data available (22).

The utility scores used to value these health conditions are as follows:

- Before surgery = 0.8- After surgery = 0.49- After fracture = 0.28- After amputation = 0.39

Regarding costs, the average cost per patient only for Cerament-G and for the innovative strategy group was estimated at 2,664 € (based on the assumption of using 15 ml of product for a third of patients and 10 ml for the remaining two-thirds). The average cost of a hospital stay was estimated, according to the French study on cost taking into account the different levels of severity, at €13,776 for a leg amputation and at €3,330 for a broken leg. Finally, the cost of a recurrence of infection was estimated, according to an expert, at approximatively €10,000.

The average cost difference hypothesis was €1,144, with a standard deviation at €1,000, and the average difference of QALY hypothesis was 0.04, with a standard deviation at 0.03. For a maximum willingness to pay of €50,000, a correlation coefficient of −0.03, an alpha risk of 5% and a beta risk of 20%, with 10% of early withdrawal, the number of subjects needed was estimated at 196 (98 per group). As this estimate is conservative, the estimated number of subjects needed corresponds to a high value.

The randomization of 200 patients in the study will therefore validate both the efficiency and the clinical efficacy hypotheses. Finally, considering that 10% of patients whose inclusion will be invalidated by the Patient Eligibility Validation Committee, a total of 220 patients will be included.

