
Post-operatively, the patient receives a probabilistic systemic antibiotic therapy then a systemic antibiotic therapy targeted on the identified germ, for a period of 3 months. The effectiveness of these antibiotics relies on their ability to penetrate bone tissue. Despite the progress made in both antibiotics and surgical treatment, the probability of failure of this treatment (infectious recurrence) is around 20%, and has unfortunately remained stable for more than 20 years (1, 4). A single-center study published in 2018 (4) followed 116 patients for at least 1 year after discharge from hospital for treatment of osteomyelitis of the long bones of the lower and upper limbs (the class was not specified). In total, 26 infectious recurrences (22.4%) were observed with an average delay of 11.2 months (95% CI = 3.3–19.1). Recurrences could be explained by the persistence of the initial germ despite a well-conducted treatment or by superinfections with other bacteria, acquired during surgery, which took advantage of the “dead space” generated by the surgical curettage. In the event of failure, a new surgical and antibiotic sequence is often proposed, with a new risk of fracture or even amputation (approximately 5% of patients experienced treatment failure) due to bone weakening and iterative surgeries.

Local antibiotic therapy could be a solution, but so far, it has not been clearly considered and recommended due to the lack of a “carrier” or a device that could stabilize and release an antibiotic locally over several weeks.

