Cerament-G will be used in this study for the management of patients with chronic osteomyelitis in the innovative strategy, as an adjunct during surgery usually performed by corticotomy. It will be used in accordance with the indications of the CE marking and its instructions for use. The volume of Cerament-G used during the intervention will be planned according to the volume of the cavity to be filled; it is on average 15 ml and cannot exceed the maximum volume corresponding to a gentamicin concentration of 6 mg/kg of patient weight. The volume to be administered will be discussed at a meeting of the eligibility validation committee, which will propose an optimal volume given the characteristics of the patient. In the event of a very large defect, the use of part of the volume of Cerament-G to form beads (or pellets) may be proposed, which would contribute to the best possible filling while limiting the total volume to be used.

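### The 196 patients and 80% power stated for the primary cost-utility outcome do not follow from the printed planning inputs

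*Protocol article*

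**What the plan says.** All references are to the protocol article. Section 2.5 makes the incremental cost-utility ratio at 24 months the primary outcome. Section 2.10.1 (Sample size calculation) first sizes the trial on recurrence, giving 100 per group after 10% withdrawal, and then adds a cost-utility calculation.

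The cost-utility inputs are:

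- Recurrence: "6% in the innovative strategy vs. 20% in the standard of care".
- Fracture and amputation: "fractures and amputations (5% in both groups) have been taken into account". No denominator is named.
- Durations: "utility is decreased 6 months before revision surgery, 3 months after revision surgery, 9 months after amputation and 3 months after fracture".
- Utilities: 0.8 before surgery, 0.49 after surgery, 0.28 after fracture, 0.39 after amputation.
- Costs: €2,664 for the device, €10,000 for a recurrence, €13,776 for an amputation, €3,330 for a fracture.

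The resulting assumptions are: "The average cost difference hypothesis was €1,144, with a standard deviation at €1,000, and the average difference of QALY hypothesis was 0.04", with an SD of 0.03 for QALYs, a threshold of €50,000 per QALY, a correlation of −0.03, alpha 5%, beta 20% and 10% withdrawal. The result is 196 patients. The section adds: "As this estimate is conservative, the estimated number of subjects needed corresponds to a high value". It concludes that randomising 200 patients will serve both the efficiency and the clinical hypotheses.

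The device cost rests on "15 ml of product for a third of patients and 10 ml for the remaining two-thirds". Section 2.4.1 (Study treatments) says of the volume planned for use that "it is on average 15 ml".

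**The concern.** A reader who puts the printed inputs into the usual net-benefit formula does not get 98 per group, and cannot tell from the section which input is at fault. Rebuilding the two differences also requires a reading of the 5% that the section leaves open: if it means all patients in each arm, fractures and amputations cancel and contribute nothing.

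This matters because the net benefit is a small difference between two larger amounts. At €50,000 per QALY, a change of 0.001 QALY moves it by €50, so rounding at the second decimal is not harmless. What is at stake is whether the power claimed for the primary outcome is correct.

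**Working it through.** **1. The plan's own figure.** With incremental net benefit INB = 50,000 × ΔQALY − ΔCost:

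- INB = 50,000 × 0.04 − 1,144 = €856.
- SD² = (50,000 × 0.03)² + 1,000² − 2 × (−0.03) × 1,500 × 1,000 = 3,340,000, so SD = €1,828.
- n per group = 2 × (1.96 + 0.84)² × SD² / INB² = 72, or 80 with 10% withdrawal (160 in total).

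Sidedness is not stated for this calculation; one-sided gives 57, or 63 to 64 with withdrawal. Neither gives 98.

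With a correlation of −0.3 and everything else as printed, SD² = 4,150,000, SD = €2,037 and n = 89. Then 89 × 1.1 = 97.9, which rounds up to 98 (89 / 0.9 gives 99). This matches the stated figure, but a misprint is an inference.

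**2. The cost difference.** The difference in recurrence is 0.20 − 0.06 = 0.14.

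- 5% of all patients in each group: the events cancel, and ΔCost = 2,664 − 0.14 × 10,000 = €1,264.
- 5% each for amputation and fracture among patients with recurrence: ΔCost = 2,664 − 0.14 × (10,000 + 0.05 × 13,776 + 0.05 × 3,330) = 2,664 − 0.14 × 10,855.3 = €1,144.26.

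Only the second gives the stated €1,144.

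**3. The QALY difference on the same reading.** The utility outside the listed states is not given. Taking it as 1.0 (an assumption):

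- Recurrence: 0.5 × (1 − 0.8) + 0.25 × (1 − 0.49) = 0.2275.
- Amputation: 0.75 × (1 − 0.39) = 0.4575.
- Fracture: 0.25 × (1 − 0.28) = 0.18.
- ΔQALY = 0.14 × (0.2275 + 0.05 × 0.4575 + 0.05 × 0.18) = 0.0363.

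A lower reference utility gives a smaller difference: 0.031 at 0.95 and 0.025 at 0.9, both of which round to 0.03. A value at or very near 1.0 is therefore the one consistent with the stated 0.04, and even then 0.04 is reached only by rounding up.

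**4. Effect of the rounding.** Unrounded, INB = 50,000 × 0.0363125 − 1,144.26 = €671. Two-sided, with 200 randomised and 10% loss (90 evaluable per group):

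| ΔQALY | Correlation | n per group before withdrawal | Power at 90 per group |
|---|---|---|---|
| 0.04 | −0.03 | 72 | 88% |
| 0.04 | −0.3 | 89 | 80% |
| 0.0363 | −0.03 | 117 | 69% |
| 0.0363 | −0.3 | 145 | 60% |

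**5. Volume.** The costing mix has a mean of (15 + 10 + 10) / 3 = 11.7 ml. Section 2.4.1 gives 15 ml.

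**6. The clinical calculation.** 6% against 20%, two-sided 5%, 80% power, gives 90 per group without continuity correction, and 100 after 10% withdrawal. This agrees with the plan.

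**The case against.** The strongest reply is that the planning differences are sound. Applying the 5% to recurrences reproduces €1,144 to the euro and 0.04 at the printed precision. It also fits the Rationale (section 1.1), which speaks, after failure of treatment, of a further operation "with a new risk of fracture or even amputation (approximately 5% of patients experienced treatment failure". This stands. A reader might infer from the wording of section 2.10.1 that the 5% covers all patients, so that the differences are unsupported and the net benefit is only about €329 (50,000 × 0.03185 − 1,264). The match on €1,144 shows that the planners did not calculate that way. The defect is an unstated denominator.

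It can also be said that, on the printed inputs, 98 per group is more than needed. That is true for the rounded 0.04 and a correlation of −0.03, but it does not explain where 98 came from and does not survive removal of the rounding.

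Three further inferences go beyond the documents:

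- That the net benefit nearly vanishes with a reference utility of 0.9. That value conflicts with the plan's own 0.04.
- That a 15 ml mean would remove the net benefit. This needs a price proportional to volume, and no unit price is given for the 5 ml and 10 ml formats.
- That the claim of a conservative estimate is false. Section 2.10.1 counts only some costs, while section 2.7.2 lists others, such as rehabilitation, home help, informal care and transport. The Rationale expects savings in follow-up and rehabilitation care. The claim may rest on those omissions.

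Finally, the 200 randomised patients do not depend on the cost-utility calculation. This also stands.

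**Conclusion.** The point holds in a limited form. The stated 196 does not follow from the printed inputs: they give about 160, and a correlation near −0.3 would be needed to reach 196. The 5% lacks a denominator, although the arithmetic shows which one was used. Rounding 0.0363 up to 0.04 raises the net benefit by €184 (50,000 × 0.0036875), about 27%. Without it, power for the primary comparison at 90 evaluable per group is about 69% at the printed correlation and 60% at −0.3, not 80%. The two mean volumes contradict each other and must be reconciled; which one is right is not for this review.

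The power figures rest on the plan's own SDs and threshold, a two-sided 5% test, a reference utility of 1.0 and 10% loss. They do not show that the trial is too small for recurrence, or that the planning differences were invented.

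**What to change.** In section 2.10.1:

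- State whether the 5% applies to all patients or to those with recurrence, and that it applies to each of the two events.
- Confirm or correct the correlation, and state whether the test is one- or two-sided.
- State the reference utility, and carry the unrounded QALY difference through the formula.
- Reconcile the volume behind the device cost with the mean volume in section 2.4.1, and update the cost difference if it changes.
- Restate the power that 200 randomised patients give for the cost-utility comparison, and limit the closing statement about serving both hypotheses to what that power supports.
- If the description of the estimate as conservative is kept, say what it rests on.

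This is a change of text only. No extra patients are needed. The cost is a less favourable stated power for the primary outcome.

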A prospective study was conducted on 100 patients with chronic class III (*n* = 78) or IV (*n* = 22) osteomyelitis (105 bones) (10). The treatment was performed by one-step debridement surgery with the addition of Cerament-G, between March 2013 and February 2015, with a postoperative follow-up of 12 to 34 months (19.5 months on average). An infectious recurrence was observed in 4 patients between 145 days (approximately 5 months) and 563 days (approximately 18 months), all class III (i.e., 5%, 4/78). Recurrence was defined by a positive culture following a biopsy or an aspiration guided by radiology. Eleven patients presented with a minor extraosseous leakage of Cerament-G, visible on radiology, without consequences for the patients. In 6 cases, white wound drainage fluid, with the appearance of liquefied calcium sulphate residues, was observed.

A second prospective non-randomized monocentric study compared 3 antibiotic-impregnated bone substitutes as an adjunct to surgery for the treatment of patients with class III or IV chronic osteomyelitis (11): Septocoll-E (*n* = 74, mean follow-up 1.75 years); Osteoset-T (*n* = 166, mean follow-up 1.96 years); and Cerament-G (*n* = 73, mean follow-up 1.78 years—including 64 class III patients). The infectious recurrence rate for the group treated with Cerament-G was 4.1% (3 patients). In this group, the fracture rate was 1.4% and the leak rate 9.6%. These results were lower than those observed in the other groups (notably twice as low as in the Osteoset-T group; statistically significant differences), despite a percentage of patients presenting a higher risk of recurrence.

Cerament-G is a potential breakthrough innovation in the management of chronic osteomyelitis, but its use is limited in France due to its high cost (up to about €4,000 per procedure depending on the dose), which is not covered by the national health insurance.

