#### Study treatments

2.4.1.

Cerament-G is an absorbable ceramic bone substitute composed of calcium sulfate, hydroxyapatite, and gentamicin sulfate, intended to fill bone gaps and deficits in the skeleton and promote bone healing. This is a medical device with CE marking since February 11, 2013, and manufactured by the Bonesupport laboratory (Lund, Sweden). The product, supplied in 5 ml or 10 ml format, consists of a powder and a liquid component. The powder contains 40% hydroxyapatite and 60% calcium sulfate hemihydrate. The liquid component is saline solution and gentamicin. The mixture of the components gives a viscous material suitable for direct or percutaneous injection into a bone void. By combining hydroxyapatite and calcium sulfate, an optimal balance is achieved between the rate of implant resorption and the rate of growth in bone. Calcium sulfate acts as an absorbable carrier for hydroxyapatite. Hydroxyapatite, a substance with a low resorption rate and a high osteoconductive profile that promotes bone growth, provides long-term structural support for new bone tissue. The hardened material facilitates bone growth and based on the observation of serial x-rays in a large number of patients and various conditions, it appears to be replaced by bone over a period of 6 to 12 months.

Cerament-G mixed contains 17.5 mg of gentamicin per ml of paste. Gentamicin prevents colonization of microorganisms sensitive to gentamicin in order to protect bone healing. Gentamicin is bactericidal against a wide range of bacterial infections, mainly Gram-positive bacteria like Staphylococcus, but also many Gram negative bacteria including Pseudomonas, Proteus, Serratia, which are also found in chronic osteomyelitis.

Cerament-G is indicated for use as a bone void filler material in a surgical procedure where there is a risk of bacterial contamination. It is therefore indicated to fill gaps and bone deficits in the skeleton that do not involve the stability of the bone structure, especially in the limbs. These bone defects may appear spontaneously or have been created surgically or following trauma to the bone, have been identified during primary surgery or surgical revision. It can also be bone defects identified around rigid implant devices.

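### The device cost behind the economic sample size assumes a mean of 11.67 ml of Cerament-G, but the treatment section gives a mean of 15 ml

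*Protocol article*

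**What the plan says.** Sample size calculation (Protocol article, 2.10.1) states that "the average cost per patient only for Cerament-G and for the innovative strategy group was estimated at 2,664" euros, "based on the assumption of using 15 ml of product for a third of patients and 10 ml for the remaining two-thirds". It then gives a mean cost difference of €1,144 (SD €1,000), a mean QALY difference of 0.04 (SD 0.03), a willingness to pay of €50,000, a correlation of -0.03, alpha 5%, beta 20% and 10% withdrawal. From these it reports 196 patients (98 per group), calls the estimate conservative, and concludes: "The randomization of 200 patients in the study will therefore validate both the efficiency and the clinical efficacy hypotheses".

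Study treatments (2.4.1) says the volume is planned from the cavity to be filled, and that "it is on average 15 ml and cannot exceed the maximum volume corresponding to a gentamicin concentration of 6 mg/kg of patient weight".

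Three other statements bear on price:
- Study treatments: "The product, supplied in 5 ml or 10 ml format".
- Rationale (1.1): the cost is "up to about €4,000 per procedure depending on the dose".
- Cost evaluation (2.7.2): the trial will value "the medical device from its non-negotiated acquisition price".

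No price per pack or per ml is given.

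**The concern.** The two sections describe the same quantity, the volume of product used per patient, and give different means. A mix whose largest value is 15 ml cannot average 15 ml.

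The costed volume is the lower one, so the error, if it lies in the costing, makes the plan too favourable to the device. The economic calculation concerns the primary outcome, the incremental cost-utility ratio at 24 months. At stake is the part of the sample-size conclusion that says 200 patients will settle the efficiency hypothesis.

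**Working it through.** **1. The two volumes.** Sample size calculation: (1/3)(15) + (2/3)(10) = 11.67 ml. Study treatments: 15 ml.

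The gentamicin cap does not reconcile them. At 17.5 mg/ml, 15 ml carries 262.5 mg, which 6 mg/kg allows from 262.5/6 = 43.75 kg. At an assumed 70 kg the cap is 420/17.5 = 24 ml, so volumes above 15 ml are permitted, yet the costing has none. Nor can the 15 ml be read as cavity volume, because the same clause limits it by gentamicin dose, which only the product has.

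**2. Reproducing the plan's cost difference.** Recurrence is 20% versus 6%, a difference of 0.14. A recurrence costs €10,000. Amputation (€13,776) and fracture (€3,330) are each taken at 5%, here per recurrence, because that reading reproduces the printed figure.

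- Offset = 0.14 × (10,000 + 0.05 × 13,776 + 0.05 × 3,330) = 0.14 × 10,855.3 = €1,519.7
- Cost difference = 2,664 - 1,519.7 = €1,144, as printed
- Implied net benefit = 50,000 × 0.04 - 1,144 = €856 (not printed, but it follows)

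Each extra euro of device cost therefore removes one euro of net benefit.

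**3. Device cost at a mean of 15 ml.** Let X be the price of a 10 ml pack, rX that of a 5 ml pack, and p the share of patients who need a 5 ml pack. Assume whole packs and at most one 5 ml pack per patient.

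- Plan's mix: X(1 + r/3) = 2,664
- Mean of 15 ml: cost = X(1.5 + (r - 0.5)p)

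The second exceeds the first for any r above 0 and below 1.5, whatever p is. The direction therefore does not depend on the exact price; the size does. The range r = 0.5 to 1.0 is my assumption.

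| Case | X | Device cost | Cost difference | Net benefit | Cost per QALY |
|---|---|---|---|---|---|
| Plan (11.67 ml) | – | €2,664 | €1,144 | €856 | €28,606 |
| r = 1, half at 10 ml and half at 20 ml (p = 0) | €1,998 | €2,997 | €1,477 | +€523 | €36,931 |
| r = 0.5, price proportional to volume | €2,283 | €3,425 | €1,905 | about €95 | €47,635 |
| r = 1, all at 15 ml (p = 1) | €1,998 | €3,996 | €2,476 | -€476 | €61,906 |

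The one price anchor, about €4,000 per procedure, points to the upper end of the ratio range. As a 15 ml procedure, X(1 + r) = 4,000 with X(1 + r/3) = 2,664 gives r = 1.004. As a 20 ml procedure, 2X = 4,000 gives r = 0.996. Proportional pricing gives €3,425 at 15 ml and €4,567 at 20 ml, and neither matches.

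**4. Power.** SD of net benefit = √[(50,000 × 0.03)² + 1,000² - 2(50,000)(-0.03)(0.03)(1,000)] = √3,340,000 = €1,828. With 90 evaluable per group (100 less 10%), SE = 1,828 × √(2/90) = €272. Normal approximation, two-sided 5%:

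- €856: power 88%
- €523: power 48%
- €95: power about 5%
- -€476: the planned effect has the wrong sign, so efficiency is not supported

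A power of 80% needs about 2.80 × 272 = €763. A device-cost rise of 856 - 763 = €93 (3.5%) uses up the margin.

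**5. A side note on the 98 per group.** The printed inputs give 72 per group, or 80 with 10% withdrawal. A correlation of -0.3 gives 89, and 98 with 10% added. At -0.3 the power figures for €856 and €523 are 80% and 41%. This is a separate matter, and the volume point does not rest on it.

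**The case against.** The best defence is that the costing paragraph is the deliberate assumption, with an explicit distribution, while the 15 ml is one clause in a device description. If that clause is the loose one, the €2,664, €1,144 and €856 all stand and only one number in Study treatments changes. This is a fair reading, and nothing in the article excludes it.

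Second, the plan calls its estimate conservative and counts only the device, recurrence hospitalizations and a few short-term utility effects. Rehabilitation, outpatient care, drugs, transport and informal care are left out. At proportional price the extra €761 (3,425 - 2,664) would be offset by 761/0.14 ≈ €5,440 more saved per avoided recurrence, or about €15,400 in place of €10,000. The Rationale puts one hospital stay for an osteoarticular infection at €5,518 to €19,608, so an offset is possible. But the remark is not quantified, and the stated 80% power was computed without those savings. It does not resolve the conflict.

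Third, little in the trial's conduct depends on this. The sample size is based on recurrence, the article itself calls the economic estimate uncertain, device cost will be measured by micro-costing, and deterministic sensitivity analyses are planned. All of this stands and sets the weight of the point.

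A reader might infer that planned net benefit is really €95. That takes Study treatments as correct and price as proportional to volume, which does not fit the article's price anchor. Under the assumed price range even the sign is open.

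**Conclusion.** The inconsistency is real and unreconciled: 15 ml in one section, 11.67 ml in the other. If 15 ml is right, device cost is about €3,000 to €4,000, net benefit lies between about +€523 and -€476, and power for the efficiency hypothesis is at most about 48% with the printed correlation and 90 evaluable per group. These figures assume a pack-price ratio of 0.5 to 1.0, whole packs and all other planning inputs unchanged. They show how far the planning claim depends on the volume; they do not forecast the trial's result.

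A reader might also infer that 200 patients are too few. The documents do not support that. Recurrence of 20% versus 6% at two-sided 5% and 80% power needs 90 per group, or 100 with 10% withdrawal, and device volume plays no part in it. The planning volume also enters no analysis. What is unsupported, if 15 ml holds, is the efficiency half of the statement that 200 patients validate both hypotheses. The weight is minor.

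**What to change.** State one expected mean volume in Study treatments and in Sample size calculation.

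- If it is 15 ml: recompute mean device cost from actual pack prices and the expected volume mix, carry it through to the cost difference, net benefit and economic power, and restate or withdraw the claim that 200 patients validate the efficiency hypothesis. If the estimate is still called conservative, give the omitted savings a figure.
- If it is 11.67 ml: correct the mean in Study treatments; the costing stands as far as volume is concerned.

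The cost is a wording change and one recalculation from prices that the sponsor can obtain. Enrolment, data collection and analysis stay as they are.
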